## Discussion

### Progress of the study

Between July 2004 and November 2005, a total of 717 eligible patients were selected for inclusion from six Heart Failure and/or Cardiology Outpatient Clinics, 339 of whom (47.3%) signed the informed consent form and underwent the baseline assessment (see figure 2). The remaining 378 patients refused or were unable to participate in the study for various reasons: for example, 84 patients did not participate because of physical health problems, 74 patients were not interested or felt no need to participate, and another 74 patients had no time or opportunity to participate (see figure 2). After completion of the baseline assessment, 318 patients were included in the trial; 187 patients were allocated to the intervention group and 131 to the control group.

We had calculated that the study would require a sample size of 2 × 180, including a 30% drop-out rate. A total of 187 patients were allocated to the intervention group, which was according to plan. The number of patients allocated to the control group (n = 131), however, was smaller than planned. At present, follow-up data are being collected. The exact drop-out rate and related consequences for the power calculation will become clear after completion of the data collection in January 2007.

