### Randomisation

In each cycle, patients were randomised after completion of the baseline measurement if a sufficiently large group of eligible patients per hospital could be formed. We decided that at least eight patients per group had to be allocated to the intervention group, because CDSMP classes normally consist of at least eight participants, for reasons of group dynamics [16]. Eligible patients therefore had a slightly higher chance to be allocated to the intervention group (59%) than to the control group (41%) during the total recruitment period. The maximum number of patients allocated to each CDSMP class was set at 14. The randomisation procedure was performed by an independent researcher by random computerised allocation using SPSS 12.0 for Windows.

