### Power calculation

The sample size calculation was based on figures derived from Dutch research among newly diagnosed older CHF patients [21] relating to one of the primary outcome variables in the present study, general self-efficacy expectancies (GSES by Sherer and colleagues [20]). To detect a mean difference of at least 4.0 points in general self-efficacy expectancies between the intervention and control groups (SD = 11.8; equivalent to an effect size of 0.34), at least 137 patients in both the intervention and control groups were required to achieve a power of 80% at an alpha of 0.05 (one-sided). Assuming a drop-out rate of 30% during the trial, a total of 2× 180 patients have to be included in the study.

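### Power is stated for two equal arms of 180, but 187 and 131 were allocated, and no projected power is given for those numbers: at the assumed 30% drop-out it is about 70% two-sided or 80% one-sided.

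*Protocol article*

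**What the plan says.** The Power calculation section works from one primary outcome, general self-efficacy (GSES). Its aim is "To detect a mean difference of at least 4.0 points in general self-efficacy expectancies between the intervention and control groups", with "SD = 11.8; equivalent to an effect size of 0.34". It says that "at least 137 patients in both the intervention and control groups were required" to reach "a power of 80% at an alpha of 0.05 (one-sided"). It then moves to 2 × 180 enrolled: "Assuming a drop-out rate of 30% during the trial".

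The Randomisation section explains that each class needed at least eight intervention patients. Eligible patients therefore had a "slightly higher chance to be allocated to the intervention group (59%) than to the control group (41"%).

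Under Progress of the study, 318 patients are reported as included, 187 in the intervention arm and 131 in the control arm. The section recalls the target ("We had calculated that the study would require a sample size of 2 × 180, including a 30% drop-out rate") and says that the control arm came out smaller than planned. It closes with: "The exact drop-out rate and related consequences for the power calculation will become clear after completion of the data collection in January 2007".

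**The concern.** The only power statement in the article belongs to a design that was not delivered. It assumes equal arms and 360 patients; the trial has unequal arms and 318. The control arm, at 131, is below the stated per-arm minimum of 137 before anyone drops out. The article recognises the problem but puts no figure on it, although the difference, SD, alpha, assumed drop-out and final allocation are all stated.

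At stake is how a non-significant result on self-efficacy will be read. If 80% remains the only figure on record, a reader may take such a result as stronger evidence against a 4.0-point effect than the numbers allow. Whether there is a real shortfall depends on whether the test is one-sided or two-sided, and the article's own figures disagree on that.

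**Working it through.** **Inputs, all from the protocol article.** Difference δ = 4.0, SD σ = 11.8, alpha 0.05, power 80%, 137 per arm, drop-out 30%, 2 × 180 planned (Power calculation); 187 and 131 allocated (Progress of the study).

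**Step 1: reproduce 137.** With equal arms, n per arm = 2(z_α + z_β)²σ²/δ².
- Two-sided 0.05: 2 × (1.960 + 0.842)² × 11.8²/4.0² = 136.6, so 137. This matches.
- One-sided 0.05, as labelled: 2 × (1.645 + 0.842)² × 11.8²/4.0² = 107.6, so 108. This does not match.

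The stated 137 is therefore a two-sided number carrying a one-sided label.

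**Step 2: power at the achieved allocation.** SE = σ√(1/n₁ + 1/n₂), and power = Φ(δ/SE − z_α). At 30% drop-out the evaluable numbers are 187 × 0.7 = 130.9 and 131 × 0.7 = 91.7.
- SE = 11.8 × √(1/130.9 + 1/91.7) = 1.607, and 4.0/1.607 = 2.489.
- Two-sided: Φ(2.489 − 1.960) = 70.2% (noncentral t: 69.8%).
- One-sided: Φ(2.489 − 1.645) = 80.1% (noncentral t: 79.9%).
- Difference detectable with 80% power, two-sided: (1.960 + 0.842) × 1.607 = 4.5 points.

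| Drop-out | Evaluable | Two-sided power | One-sided power |
|---|---|---|---|
| 0% | 187 / 131 | 84.5% | 90.8% |
| 10% | 168.3 / 117.9 | 80.6% | 88.1% |
| 20% | 149.6 / 104.8 | 75.8% | 84.5% |
| 30% | 130.9 / 91.7 | 70.2% | 80.1% |

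**Step 3: drop-out that can be tolerated.** The equal-arm equivalent of 187/131 is 2 × 187 × 131/318 = 154.1 per arm. Two-sided, 1 − 136.6/154.1 = 11.3%. One-sided, 1 − 107.6/154.1 = 30.2%.

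**Step 4: where the loss comes from (two-sided, 30% drop-out).**
- As planned, 180 × 0.7 = 126 per arm: SE = 11.8 × √(2/126) = 1.487, power 76.7%. The planned 2 × 180 was thus already short of 137 evaluable. It is close to 137 × 1.3 = 178.1, whereas 137/0.7 = 195.7, or 196.
- 318 patients split equally, 159 × 0.7 = 111.3 per arm: SE = 11.8 × √(2/111.3) = 1.582, power 71.5%.
- 318 patients split 187/131: power 70.2%.

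The imbalance itself costs little. Most of the fall comes from the smaller total and from the way drop-out was added.

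**Step 5: baseline adjustment.** The Analysis section plans to adjust for baseline scores. If the baseline-to-follow-up correlation is ρ, the SE becomes 1.607 × √(1 − ρ²). The article gives no ρ, so these values are assumed. Two-sided power at 30% drop-out is 78% for ρ = 0.4, 82% for ρ = 0.5 and 88% for ρ = 0.6.

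**The case against.** The strongest reply is that the article states a one-sided alpha, and on that basis the trial at 30% drop-out sits on its 80% target. That stands: a reader might infer that the trial simply has 70% power, and the document does not support this without three conditions (two-sided, unadjusted, 30% drop-out). What keeps the two-sided figure relevant is that the article's own 137 can be obtained in no other way.

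Three further inferences should be resisted.
- **131 is below 137, so power is lost.** Not by itself. The larger intervention arm compensates, and before drop-out power is above 80% on either basis.
- **The closing sentence announces a post-hoc power analysis.** It does not. It says that the exact drop-out rate and what follows from it are not yet known, which is true. Nothing suggests that power will be computed from the observed effect. Updating the calculation for realised drop-out, with the planned difference and SD, is acceptable.
- **The SD is wrong because it comes from newly diagnosed patients, while this trial requires CHF for at least six months.** The source is openly stated, and nothing in the article shows that the SD differs or by how much.

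It is also fair to say that the article discloses the shortfall and does not claim that 80% still holds, and that baseline adjustment may restore power. These points limit the seriousness of the matter. They do not supply the missing projection.

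**Conclusion.** The point holds in a limited form. The published power statement describes 2 × 180, the trial has 187/131, and nothing replaces the statement although every planning input is given. At the assumed 30% drop-out, unadjusted power for 4.0 points is about 70% on the two-sided basis that yields 137, and about 80% on the one-sided basis as labelled. The ten-point gap between these cannot be resolved from the article, so settling the sidedness comes first.

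The figures assume SD 11.8, equal drop-out in both arms and no clustering by class, for which no value is given. With baseline adjustment, two-sided power could be about 78% to 88% under assumed correlations of 0.4 to 0.6. This is an inexpensive correction to a figure on which the trial relies. It does not show that the trial is inadequate.

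**What to change.** 1. Reconcile the one-sided label in the Power calculation section with the 137 per arm, and state which sidedness the analysis will use.
2. Replace the statement of 80% power at 2 × 180 with projected power at 187/131 for drop-out of 10 to 30%: 80.6% to 70.2% two-sided, or 88.1% to 80.1% one-sided. Note that the planned baseline adjustment may recover power, and give the assumed correlations.
3. State that non-significant results will be read through the 95% confidence interval for the difference, set against 4.0 points.
4. Keep the later update for realised drop-out, stating that it uses the planned difference and SD.

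The cost is a short recalculation and some rewording. The stated figure becomes less favourable, at least on the two-sided basis. No patients are added.
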